### Outcome Measures

#### Overview

All subjects will complete several commonly used instruments to assess their level of disability and neck pain. The primary outcome measure will be the NDI to capture the effect of treatment on the level of disability. Secondary outcome measures will include the Visual Analog Scale (VAS) to assess pain, the Global Rating of Change Scale (GROC) to measure the patient’s perceived recovery, the patient perception of the intervention to determine if they felt they received the genuine dry needling intervention, and patient expectations to determine which treatments they believed would be most beneficial for their current condition. The self-report measures that will be used include those discussed in the following sections.

#### Primary Outcome

The NDI was created to measure pain-related disability associated with activities of daily living in people with neck pain [45,46]. The NDI contains 10 focused sections. Each item is scored on a 6-point scale and can reach a maximum score of 5; therefore, the maximum score is 50. This score will be calculated as a percentage, with higher scores indicating higher levels of disability [46]. Content, construct validity, and reliability of the NDI has been previously shown in patients with neck pain [46,47]. The NDI has been used by researchers to evaluate the effect of treatments on patients’ perceived levels of functioning and disability [48-51].

#### Secondary Outcomes

##### Visual Analog Scale

The VAS is a single-item measure of pain using a 100-mm horizontal line anchored on the left side, which represents *no pain*, while the right side represents *the worst pain imaginable*. Patients mark a score by making a vertical line where they feel best represents their pain intensity. The VAS has been shown to be reliable [52] and valid [53].

##### Patient Global Rating of Change

The GROC will be used, which is a 15-point global rating scale described by Jaeschke et al [54]. The scale ranges from –7 (*a very great deal worse*) to zero (*about the same*) to +7 (*a very great deal better*). The global rating will be administered at the follow-up examinations only.

##### Patient Perceptions

Patient perceptions about the intervention will be used to determine whether the sham was an effective placebo. Patients will be asked for their perceptions on the dry needling intervention they received in order to determine if they felt they received genuine treatment. The following questions will be asked: What did you think of the dry needling intervention? Would you be willing to have the dry needling intervention again if you were attending physical therapy? Do you think you received the real dry needling intervention?

##### Patient Expectations

Patient expectations will be assessed at enrollment into the trial. Patients will be asked to rate each intervention on a 5-point Likert scale as to whether they believe each specific intervention will significantly help to improve this episode of their neck pain.

All outcome assessments will be performed by an individual blind to group assignment and will be performed at baseline, 4 weeks, 6 months, and 12 months. The latter two assessments will be mailed to the patients to improve return rate (see Table 1) [55].

**Table 1 table1:** Summary of outcome measures and time points for collection.

Outcome measure	Baseline	4 weeks	6 months	12 months
Neck Disability Index	Yes	Yes	Yes	Yes
Visual Analog Scale	Yes	Yes	Yes	Yes
Global Rating of Change	No	Yes	Yes	Yes
Patient perception of intervention	No	Yes	Yes	Yes
Patient expectations	Yes	No	No	No

### Intervention

#### Overview

Once the baseline examination is complete, equal numbers of patients will be randomly assigned to one of two groups: (1) manual therapy, exercise, and dry needling (MTEX-Needle group) or (2) manual therapy, exercise, and sham dry needling (MTEX-Sham group). A random-number generator will be used to conduct the randomization. The randomization procedure will be conducted prior to the initiation of the study using a computer program randomizer by an individual not involved in patient recruitment. The randomization will be concealed according to the following procedure. The group assignment will be recorded on a label that will be placed inside an envelope and the envelope will be sealed. After the baseline examination is complete, the randomization envelope will be handed to a treating therapist and treatment will begin according to group assignment. Treatment will be initiated immediately following the baseline examination, unless prohibited by time constraints; in this case, the patient will be scheduled for a follow-up session within 3-5 days to receive the first treatment. Patients in both groups will attend physical therapy for seven treatments over a maximum of 4 weeks. Each treatment session will last for a total of 45 minutes of one-on-one treatment time with the treating physical therapist.

To ensure that the clinicians involved in administering the treatment are familiar with the procedures of the study, they will be required to participate in a 2-hour training session. During the training session, the manual therapy, exercise, and dry needling techniques will be reviewed to ensure treatments are applied in a standardized manner consistent with the treatment algorithm outlined below. The majority of the training time (ie, 1 hour) will be dedicated to ensuring standardization of the application of the dry needling and sham needling techniques. The second hour will be spent reviewing the manual therapy techniques, therapeutic exercises, and algorithms to help standardize their prescription, as well as data collection procedures. Due to the pragmatic nature of this study design, even when the treatment algorithm is followed for manual therapy and exercise, there will likely be some variation in the interventions selected by each therapist based on each patient’s relevant examination findings. As this is a pragmatic trial designed to mimic usual clinical practice, this individualization of a patient’s treatment is acceptable and expected. All therapists applying all interventions will be licensed physical therapists who have also completed the required postgraduate training that enables them by their state practice act to utilize dry needling, and who regularly use the technique in practice.

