## Methods

### Design

We will conduct a randomized, double-blind, placebo-controlled trial according to the CONSORT guidelines (see Figure 1) [42,43]. Approval by both the Institutional Review Board at Concord Hospital (Concord, NH, USA), where the trial will be performed, and the University of Newcastle Human Research Ethics Committee (Callaghan, Australia), where the primary author ([name]) is currently enrolled as a PhD candidate, have been obtained. Consecutive subjects presenting to Concord Hospital physical therapy clinics (Concord, NH, USA) and Franciscan St. Francis Health physical therapy clinics (Indianapolis, IN, USA) with mechanical neck pain will be screened for eligibility criteria.

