	After needle is removed, pressure with a cotton ball will be maintained to prevent excessive bleeding
	The number of sites and specific muscles treated will be recorded by the therapist
Trigger point assessment performed on the suboccipital muscles	Patient in prone, therapist identifies the hypersensitive spot in the suboccipital muscles
	The overlying skin will be cleansed with alcohol
	Once the needle has been inserted manually into the trigger point, the needle will be pistoned in an up-and-down fashion so that 2- to 3-mm vertical motions occur (ie, fast-in and fast-out technique as described by Hong) at approximately 1 Hz for 25-30 seconds, with the aim of eliciting local twitch responses
	After needle is removed, pressure with a cotton ball will be maintained to prevent excessive bleeding
	The number of sites and specific muscles treated will be recorded by the therapist

We will compare baseline variables between groups by using independent *t* tests or Mann-Whitney U tests for continuous data and chi-square tests of independence for categorical data. An intention-to-treat analysis will be utilized, in which all participants will be analyzed in the group to which they were originally assigned. All dropouts and the reasons for dropping out of the study will be reported. An a priori alpha level of .05 will be used for all analyses. All data will be checked to ensure they meet the assumptions for the inferential statistical analyses described below. If they do not meet the necessary assumptions, appropriate nonparametric procedures will be utilized. We will examine the primary aim with a two-way repeated-measures analysis of variance with treatment group (ie, manual therapy, exercise, and dry needling vs manual therapy, exercise, and sham dry needling) as the between-subjects independent variables and time (ie, baseline, 4 weeks, 6 months, and 12 months) as the within-subjects independent variable. The hypothesis of interest is the two-way group × time interaction. Bonferroni-corrected post hoc tests will be used to determine difference between group means.

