### Power Analysis

Sample size and power calculations were performed using G*Power version 2 statistical software (Heinrich-Heine- Universität Düsseldorf) based on the minimal clinical improvement of 12 points on the NDI [51,69], assuming a standard deviation of 16 points, two-tailed, and an alpha level of .05. This requires a minimum sample size of 29 subjects per group. A total of 76 patients with a primary complaint of neck pain who meet the inclusion/exclusion criteria and consent to participate will be enrolled into the study. This sample size will yield greater than 80% power to detect both statistically significant and clinically meaningful changes in the NDI; additionally, this will control for dropouts prior to the 4-week follow-up.

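### Two clinics recruit and treat, but the primary NDI model contains only group and time; adding site with its time interaction would protect precision at almost no cost

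*Protocol article*

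**What the plan says.** **Sites.** Methods, Design names Concord Hospital clinics in New Hampshire as one source of patients. For the second it says that consecutive subjects at "Franciscan St. Francis Health physical therapy clinics (Indianapolis, IN, USA) with mechanical neck pain will be screened for eligibility criteria". The Discussion confirms two large clinics in different locations, chosen to speed recruitment.

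**Allocation.** Intervention, Overview says that "equal numbers of patients will be randomly assigned to one of two groups". The list is computer-generated before the study by someone not involved in recruitment, and concealed in sealed envelopes. The treating therapist receives the envelope and delivers the arm inside it. The text does not say how many lists there are or whether they are stratified.

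**Therapists.** The same section requires therapists to be licensed, to use the technique regularly, and to have "completed the required postgraduate training that enables them by their state practice act to utilize dry needling". All attend one 2-hour session. Therapist-level variation in manual therapy and exercise is expected and accepted. Limitations adds that individualised needling may lead to variation that masks a difference between groups.

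**Model.** Data Analysis sets treatment group as the between-subjects factor and "time (ie, baseline, 4 weeks, 6 months, and 12 months) as the within-subjects independent variable", with the group by time interaction as the hypothesis of interest. The abstract repeats this. Neither mentions site.

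**The concern.** Patients, background care and, presumably, therapists differ between two clinics in two states. The authors themselves foresee variation between therapists that could obscure the treatment effect. The model has no term to absorb it.

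Two consequences follow if NDI change differs by site. First, the site difference stays in the residual variance, so the group by time test is less precise than it could be. Second, if one arm happens to hold more patients from the better-performing site, the treatment contrast moves by the site gap times the imbalance, and the analysis does not correct it. The article names its between- and within-subjects factors explicitly, so the absence of site from the model is a stated choice and not merely a detail left to another document.

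**Working it through.** **Inputs from the article.** The target is a "minimal clinical improvement of 12 points on the NDI"; the calculation is made "assuming a standard deviation of 16 points, two-tailed, and an alpha level of .05"; 76 patients are enrolled, so 38 per arm at 1:1.

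**Assumptions, because the article gives no site figures.** Site sizes of 38/38, 51/25 or 57/19; a site gap in NDI change of 0, 6 or 12 points; within-site SD of 16; allocation 38:38 overall without stratification.

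**Step 1: the plan's own figure.** Power Analysis states: "This requires a minimum sample size of 29 subjects per group". With d = 12/16 = 0.75, the noncentral t calculation gives 80.1% power at 29 per arm and 78.7% at 28, so 29 is reproduced. At 38 per arm it gives 89.7%.

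**Step 2: chance imbalance.** The number of needling patients at one site is hypergeometric (76 patients, 38 in the arm, site size n). With x needling patients at that site, the between-arm difference in site share is (2x − n)/38, with mean 0.

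- Sites 38/38: SD 11.5 percentage points. P(22:16 or worse) = 25.1%. P(23:15 or worse) = 10.8%; that split is a difference of 8/38 = 21.1 points.
- Sites 51/25: SD 10.9 points. P(20 points or more) = 5.0%.
- Sites 57/19: SD 10.0 points. P(20 points or more) = 3.2%.

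The lower figures for uneven sites partly reflect discreteness. With 51 or 57 patients at a site, only odd multiples of 1/38 can occur, so 20 points or more means 9/38 = 23.7 points or more. At 7/38 = 18.4 points or more, the chances are 14.2% and 11.1%. The SDs show that the underlying risk changes only modestly.

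**Step 3: shift in the contrast.** Shift = site gap × difference in site share. For a 23:15 split:

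- gap 6: 6 × 8/38 = 1.3 points (11% of the 12-point target);
- gap 12: 12 × 8/38 = 2.5 points (21%).

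**Step 4: variance and power.** Leaving site out raises the SD to √(16² + gap²/4) when the sites are equal. That gives √265 = 16.3 at a gap of 6 and √292 = 17.1 at a gap of 12. At 38 per arm the corresponding power is 88.7% and 85.6%.

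A simulation of one follow-up comparison (76 patients, unstratified, true effect 12, 20,000 runs per setting) agrees:

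| Site gap | Power without site | Power with site | Type I error without site |
|---|---|---|---|
| 0 | 89.5% | 89.0% | 4.9% |
| 6 | 88.6% | 89.4% | 5.0% |
| 12 | 85.6% | 89.4% | 5.2% |

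The mean estimate without site is 12.0 in every row. A separate simulation of the four-visit group by time test (8,000 runs per setting, within-patient correlation of 0.5 assumed) gives type I error of 4.5% to 5.4% without site, which is also close to nominal.

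**Step 5: if the list was in fact stratified.** With stratified allocation but no site term, type I error falls to 4.8% (gap 6) and 3.7% (gap 12). The test becomes conservative, and the remedy is again a site term.

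**Step 6: where site must enter.** The group by time test uses the within-subject error. A site main effect alone reduces only the between-subject error and leaves that test unchanged. The site by time interaction is what removes a site difference in change.

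**The case against.** A reader might go further and infer three things that the article does not support.

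*That there is one unstratified list.* Equal allocation fits site-specific lists just as well. A condensed article may leave list structure to the full protocol, so its silence establishes nothing.

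*That the two states set different rules for needling.* The text refers only to each therapist's state practice act. It does not say that the acts differ, and it imposes common requirements and common training.

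*That site or operator is confounded with treatment.* The patient is the unit of randomisation, and therapists are trained in both the real and the sham technique. Nothing ties an arm to a site. The simulations show an unbiased estimate and type I error near 5%. Ordinary inference already allows for chance imbalance.

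It is also fair to say that a 12-point site gap equals the whole target effect and has no support in the document, that the shift in Step 3 needs an imbalance that usually will not occur, and that power at full enrolment stays above 80% even then.

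All of this stands. What remains is that the stated model omits a known design feature that can be included for very little.

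**Conclusion.** The point holds as one of efficiency and chance imbalance, not of validity. If the sites do not differ in NDI change, nothing is lost by omitting site. With an assumed gap of 6 to 12 points, omission costs about 1 to 4 points of power at 38 per arm. A 23:15 split, which has about an 11% chance of occurring or being exceeded with equal sites and no stratification, would move the contrast by about 1.3 to 2.5 points.

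These sizes rest on assumed site sizes and gaps, and on 16 being the within-site SD. If 16 already includes variation between sites, the planned 89.7% includes that loss and a site term would be a gain over it. The power figures come from a single follow-up comparison and only approximate the four-visit interaction test.

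**What to change.** Before unblinding, add site as a fixed between-subjects factor, together with site by time, to the primary NDI model. Report the NDI treatment difference by site descriptively, without a separate test at each site.

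The cost is 1 degree of freedom per time contrast (3 for the four visits) and about 0.5 points of power if the sites do not differ. The change serves whether or not the list was stratified. Allocation need not be touched: re-issuing envelopes during recruitment is not justified, because no defect in the list is shown and the model term deals with the problem.

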#### Manual Therapy: 15 Minutes

Individuals randomized to both groups will receive manual therapy to address joint mobility of the cervical and thoracic spine. Mobilization of the cervical spine and thrust manipulation targeting the thoracic spine will occur at the beginning of each treatment. The treatment algorithm, combined with physical examination findings, will guide clinicians to allow them to determine which techniques will be used and is outlined below (see Table 2).

#### Physical Examination Techniques That Will Guide Manual Therapy Intervention

##### Cervical/Thoracic Spine Active Range of Motion and Behavior of Symptoms

The examiner will record a single range of motion measurement for flexion and extension using an inclinometer as described by Hole [56]. Bilateral rotation will be measured using a standard long-arm goniometer [57]. Reliability coefficients for cervical spine range of motion parameters range from .81-.84 (inter-class correlation [ICC] 2,1) [56]. Thoracic rotation active range of motion will be assessed qualitatively. Patients will be asked to place their hands on opposite shoulders and to rotate the trunk. Care will be taken to maintain the cervical spine in neutral while the patient rotates the trunk to the left and right as far as possible. The behavior of symptoms and the presence of side-to-side asymmetry will be recorded.

##### Spring Testing

Spring testing of the cervical and thoracic spine over the spinous processes of the vertebrae will be tested with the patient prone [58,59]. The stiffness at each segment will be judged as normal, hypomobile, or hypermobile. Interpretation of whether a segment is hypomobile will be based on the examiner’s anticipation of what normal mobility should feel like at that level and compared to the mobility detected in the segment above and below. In addition, pain provocation at each segment will be judged as painful or not painful and, if painful, whether the symptoms are local (ie, under the examiner’s hand) or referred (ie, away from the examiner’s hand). Spring testing for the neck will be performed over the spinous processes of C2-C7. Spring testing for the thoracic spine will be performed over the spinous processes of T1-T5. The reliability of spring testing from our previous work showed poor reliability in the cervical spine and fair-to-moderate reliability in the thoracic spine [60].

**Table 2 table2:** Manual intervention algorithm for treatment selection.

Assessment	Treatment
Clinicians assess cervical spine mobility and range of motion, including overpressure and repeated movements, if indicated	If hypomobility or limited range of motion is identified in the cervical spine, the therapist will utilize cervical thrust manipulation or nonthrust mobilizations; this may include central and unilateral posterior-anterior, side glides, and occipito-atlanto joint (C0-1)
	Thrust manipulations may be repeated up to two times if reassessment of the patient shows improvements in range of motion, mobility, and/or pain
	Nonthrust mobilizations generally performed two to three times ×30 repetitions at each hypomobile level and may be repeated again (two to three times ×30 repetitions) if the patient shows improvements in range of motion, mobility, and/or pain
Clinicians assess thoracic spine mobility and range of motion	If hypomobility or limited range of motion is identified in the thoracic spine, the therapist will utilize thoracic thrust manipulation and/or nonthrust manipulation (may include central and unilateral posterior-anterior techniques to the thoracic spine and ribs)
	Thrust manipulation will be used unless contraindications noted (history or self-report of osteopenia/osteoporosis, etc)
	Thrust manipulations may be repeated up to two times if reassessment of the patient shows improvements in range of motion, mobility, and/or pain
	Nonthrust manipulations generally performed two to three times ×30 repetitions at each hypomobile level and may be repeated again (two to three times ×30 repetitions) if the patient shows improvements in range of motion, mobility, and/or pain

**Table 3 table3:** Exercise intervention algorithm for treatment selection.

Assessment	Treatment	Progression
Muscular endurance of the cervical flexors was evaluated with the deep neck flexor endurance test and evaluated based on hold time in seconds	Prepare participant in supine, hook-lying position and ensure craniocervical and cervical regions are in a neutral position (support with a folded towel if necessary). Teach the craniocervical flexion action. Use instructions of “feel the back of your head slide up the bed as you nod your chin.” Goal: 10 × 10-second holds	Begin with craniocervical flexion. Cue patient to “keep chin tucked in, lift, and hold your head up.” Goal: 10 × 10-second holds
Craniocervical and cervical extensors	Patient either prone on elbows or in four-point kneeling position. Suboccipital muscles—Focus on a neutral neck position: (1) Require the participant to perform craniocervical extension (chin down) and (2) Require the participant to perform craniocervical rotation (the saying “no” action). Assess quality of movement and for smooth coordination. Goal: 3 sets of 5	Patient either prone on elbows or in four-point kneeling position. Deep cervical extensors: the craniocervical region remains in neutral and the axis of motion is now at C7. Instruct the participant to curl their neck first into flexion and then to curl their neck back to extension. The participant will often require manual facilitation to achieve the correct action. To assist in maintaining the craniocervical neutral position, let the participant imagine they have a book between their hands and they must keep their eyes on the book as they lift their head. Check that muscles such as splenius capitis are not overactive. Goal: 10 × 10-second holds
Muscle length test: upper trapezius, latissimus dorsi, pectoralis minor, pectoralis major, levator scapulae, anterior and middle scalenes, and the suboccipital muscles; also scored as tight or normal	Stretching of muscles determined to have decreased length Patient to perform 3 × 30-second stretches for each muscle Goal: 3 sets of 30-second holds for each muscle	Self-overpressure to stretching of muscles will be added as appropriate
Manual muscle tests performed for the lower trapezius, rhomboids, middle trapezius, and serratus anterior	Patient to perform exercises without exacerbation of symptoms Progressed based on patient response All patients begin with thin elastic bands Goal: 3 sets of 10	Patient will be progressed to medium, heavy, and extra heavy for resistance as appropriate, based on the patient’s ability

